****Trial registration** number:**

ISRCTN11708741; Pre-results.

Strengths and limitations of this studyProspective, randomised evaluation of a clinical service using a novel stepped-wedge cluster design which avoids contamination of trial groups, while remaining acceptable to patients and study centres.The first national, 24 hours streamlined digital histopathology service, which will support all adult kidney transplant centres in the UK and is likely to have applications beyond the trial setting.Example of a low cost ‘registry-based trial’ which uses routinely collected data and has a concomitant economic evaluation to determine cost-effectiveness.Use of two primary end points (and therefore nine possible trial outcomes) increases the possibility of an equivocal, rather than definitive result.To conserve power, the study will not be stopped early except on the grounds of patient safety.Thus, there is a risk that access to histopathology may lead to fewer kidney transplants being performed.

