#### Second primary outcome: eGFR measured at 12 months after transplant

Data were extracted on all recipients who received a kidney only transplant from deceased donors (DBD and DCD) aged ≥60 years, in the UK (excluding transplants at Cambridge) between 1 April 2014 and 31 March 2016. The median number of transplant recipients per cluster per month was 2, hence providing an average cluster-period size of 8. eGFR was calculated using the 4-variable Modification of Diet in Renal Disease (MDRD) formula using uncalibrated serum creatinine measurements,^20^ hence if missing data were present for the recipients sex, age, ethnicity and serum creatinine at 12 months, then eGFR could not be calculated (19%). The mean eGFR was 41.91 with an SD of 16.06.

A mixed linear regression model was fitted to this data, with a continuous outcome (eGFR), a fixed effect for date of transplant (which was converted into year quarter, ie, six, 4-month time periods), a random effect for cluster and a random interaction between cluster and period. From this model, the WP-ICC and CAC were calculated as 0.06 and 0.08, respectively. Assuming an average cluster-period size of 8 (=2×4 clusters), this outcome will have 89% power to detect a mean difference in eGFR of 6 mL/min (assuming a significance level of 2.5%). We checked the sensitivity of this calculation by looking at an increase, and separately a decrease, of 0.5 in the mean difference; and by varying the WP-ICC by ±0.05 and CAC by ±0.016 (which equates to ±20% of the base CAC). The trial has within the region of 80% power for all anticipated values of WP-ICC and CAC, and likely values of cluster-period sizes. The power curve, with the mean difference set as 6, is shown in figure 3B. As the CAC was particularly small, we separately explored the effects of a large CAC value (0.8) and found this had minimal impact.

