### Analysis plan

The primary outcome analyses will be performed according to the intention to treat. This will include all eligible patients for whom data have been obtained and will be analysed with respect to the treatment specified by the allocated randomisation order. The primary outcomes will be compared using two-sided tests and at a 2.5% significance level. Departures from randomisation at cluster level are defined as any cluster which does not switch to the intervention when stated in the randomisation order. A cluster is able to withdraw at any point during the trial. Per protocol analysis, which will exclude departures from randomisations and any cluster withdrawals, will also be completed for both primary outcomes of the trial. In situations where a pair of kidneys are transplanted as a ‘dual’ transplant into one recipient (eg, when the biopsy score is >4), this will be counted as half a transplant (in terms of utilisation, not as effective as performing two single transplants, but better than discard).

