#### Analysis of primary and secondary outcomes

All primary and secondary outcomes will adjust for calendar time, since the intervention is sequentially rolled out, and cluster, as participants within the same centre are not independent.

The primary aim of the study is to evaluate whether there is a difference in the use of kidneys from older donors before and after exposure to the intervention. For the first primary outcome, a logistic regression model, with random effects for cluster and cluster by period; and adjusting for period (fixed effect), will be used for the hypothesis test and to obtain the associated CI. This will be supplemented with a risk difference obtained from a binomial model with identity link, random effects for centre and centre by period; and adjusting for period (fixed effect). The absolute numbers will be presented by trial arm.

Mean eGFR values in each treatment group at 1 year will be compared using a normal regression model, adjusting for random cluster effect, random cluster by period interaction and a fixed effect for period. As eGFR at 12 months is only recorded for patients who are alive with a functioning graft at 12 months, the primary analysis will be complete case and there will be no imputation for missing values. The number of participants surviving to 12 months will be reported and of those the number who have a 12-month eGFR recorded. The adjusted mean and SD eGFR at 12 months will be reported by treatment arm, alongside the adjusted treatment difference with 95% CI and p value.

A sensitivity analysis will repeat the analysis for the second primary outcome but with the following imputations: if a patient’s graft failed within 12 months, the eGFR at 12 months will be set to the mean value for patients on dialysis in the UK (currently 8.5 mL/min/1.73 m^2^).^24^ If a patient died with a functioning graft within 12 months of transplant, the 12-month eGFR will be set to the mean value at 12 months for all UK transplant patients with a functioning transplant at 1 year (currently 49.4 mL/min/1.73 m^2^). This method assumes that deaths with a functioning graft will occur at random. Multiple imputation was considered futile as insufficient clinical data are collected at the 12-month time point to accurately impute any missing measurements.

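### The eGFR primary outcome is tested at two-sided 2.5% but its difference is to be reported with a 95% CI, which does not match that test

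*Protocol article*

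**What the plan says.** The Analysis plan section of the protocol article sets the decision level for both primary outcomes: "The primary outcomes will be compared using two-sided tests and at a 2.5% significance level". Both sample size subsections use the same level, with 85% power for the proportion transplanted on first offer and 89% power for eGFR.

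The section on analysis of primary and secondary outcomes then fixes how the eGFR result is shown: adjusted means and SDs by arm, "alongside the adjusted treatment difference with 95% CI and p value". For the first primary outcome it says that the logistic model "will be used for the hypothesis test and to obtain the associated CI", without giving a level.

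The article nowhere mentions a 97.5% interval, gives a reason for 95%, or says that the eGFR interval is descriptive only.

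**The concern.** A two-sided test at level α and a confidence interval at level 1 − α give the same answer about zero. A 2.5% test therefore pairs with a 97.5% interval. Here the article states 2.5% for the test and 95% for the interval on the same comparison, so this is a mismatch between two stated figures and not a detail left open.

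At stake is how a borderline eGFR result is read. The study hypothesis is worded as and/or, so one positive primary outcome can support a claim, and testing each outcome at 2.5% keeps the overall error near 5%. The strengths and limitations list already warns of this: "Use of two primary end points (and therefore nine possible trial outcomes) increases the possibility of an equivocal, rather than definitive result". An interval that excludes zero beside a test that is not significant adds an avoidable source of equivocation.

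**Working it through.** **Inputs, all from the protocol article.** Two-sided α of 2.5% (Analysis plan). For eGFR, from the second sample size subsection: "The mean eGFR was 41.91 with an SD of 16.06"; "the WP-ICC and CAC were calculated as 0.06 and 0.08, respectively"; "Assuming an average cluster-period size of 8"; target difference 6 mL/min. From the legend of Figure 3: 20 clusters, 5 steps, 4 clusters per step, hence 6 periods. The article does not print a standard error (SE), so it is derived here.

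**Step 1: SE at the design values.** The model has fixed period effects and random cluster and cluster-by-period effects, with σ² = 16.06² = 257.92.

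- Cluster variance: τ² = σ² × WP-ICC × CAC = 257.92 × 0.06 × 0.08 = 1.238.
- Remaining variance of a cluster-period mean: s² = σ² × [(1 − 0.06)/8 + 0.06 × (1 − 0.08)] = 257.92 × 0.1727 = 44.54.
- Design sums, with I = 20 and T = 6: U = 4 × (5+4+3+2+1) = 60; W = 4² + 8² + 12² + 16² + 20² = 880; V = 4 × (25+16+9+4+1) = 220.
- Variance = I s² (s² + Tτ²) / [(IU − W)s² + (U² + ITU − TW − IV)τ²] = (20 × 44.54 × 51.97) / (320 × 44.54 + 1120 × 1.238) ≈ 2.960.
- SE = √2.960 = 1.7205 mL/min.

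**Step 2: reproduce the stated power.** Power = Φ(6/SE − z), with 6/1.7205 = 3.487.

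- Two-sided 2.5%: Φ(3.487 − 2.241) = 89.4%, against 89% stated.
- Two-sided 5%: Φ(3.487 − 1.960) = 93.7%, which does not match.

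The stated power therefore rests on two-sided 2.5%. The same method for the first primary outcome (28% against 39%, cluster-period size 18, WP-ICC 0.03, CAC 0.92) gives 84.6% to 85.1%, depending on how the binomial variance is averaged, against 85% stated.

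**Step 3: where interval and test part.**

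- The 95% CI excludes zero when |difference| > 1.960 × 1.7205 = 3.37 mL/min.
- The 2.5% test needs |difference| > 2.241 × 1.7205 = 3.86 mL/min.
- Between the two, 0.025 < p < 0.05 and they disagree.

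The band moves with the SE but always runs from 1.960 to 2.241 SE. With 22 clusters and the same inputs the SE is 1.637 and the band is 3.21 to 3.67. With 20 clusters and the article's WP-ICC limits of 0.01 and 0.11, the SE is 1.475 or 1.932 and the band is 2.89 to 3.31 or 3.79 to 4.33.

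**Step 4: how often.** The chance of disagreement is the rejection probability at 5% minus that at 2.5%, at SE 1.7205:

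| True difference (mL/min) | 95% CI excludes 0 | Significant at 2.5% | Disagreement |
|---|---|---|---|
| 0 | 5.0% | 2.5% | 2.5% |
| 3 | 41.5% | 30.9% | 10.5% |
| 4 | 64.2% | 53.3% | 10.9% |
| 5 | 82.8% | 74.7% | 8.1% |
| 6 | 93.7% | 89.4% | 4.3% |

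**Step 5: family-wise error, if the outcomes are independent.**

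- Both judged at 2.5%, as planned: 1 − 0.975² = 4.9%.
- eGFR judged by its 95% CI, first outcome at 2.5%: 1 − 0.975 × 0.95 = 7.4%.

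**Step 6: interval width.** 2.241/1.960 = 1.144, so a 97.5% CI is about 14% wider.

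**The case against.** The strongest reply is that the decision rule is not in doubt. The article names the test level, powers both outcomes at it and reports the p value beside the interval. Nowhere does it say that significance will be read from an interval. A 95% CI is a valid and conventional statement of precision, and the p value shows the reader on which side of 0.025 the result lies. All of this stands, and it limits the point to reporting. It does not remove the mismatch, because the article does not tell the reader that the interval and the test are meant to work at different levels.

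The band is also narrow, about 0.5 mL/min, and lies well below the 6 mL/min target. That stands too, although a benefit somewhat smaller than planned would land in it about one time in ten.

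Three stronger readings are tempting and are not supported:

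- A reader might infer that the plan lets the family-wise error rise to 9.75% (1 − 0.95²). That requires both primary outcomes to be judged by 95% intervals, and the article fixes 95% only for eGFR.
- A reader might treat the unstated interval level for the first primary outcome as a second error. The article defers full analysis details to the statistical analysis plan, and an interval associated with the test reads naturally as one that matches it.
- A reader might infer a conflict for the secondary outcomes. The article sets no interval level for them.

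**Conclusion.** The mismatch is real and confined to the eGFR primary outcome. It is a minor reporting inconsistency and not a flaw in the test: the formal decision rule, its type I error and the power are unaffected. Nor does the text support saying that the plan itself undoes the multiplicity control; that would take a reader who sets the stated test level aside and decides from the interval.

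Its size is an ambiguous band of roughly 3.4 to 3.9 mL/min, entered with probability 2.5% under no effect and about 11% at a true difference of 4 mL/min. The band in mL/min and the chances at non-zero differences rest on the derived SE of 1.72 mL/min, which uses the 20-cluster design of the power curve, whereas the article randomises 22 centres. The calculation also uses normal critical values. The realised SE will differ, but disagreement whenever 0.025 < p < 0.05 does not depend on it. The 7.4% figure assumes independent outcomes and the misreading described. The statistical analysis plan is not shown and may already settle the matter.

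**What to change.** Report the adjusted 12-month eGFR difference with a 97.5% CI, and use the same level for the odds ratio and risk difference of the first primary outcome so that the two primary results are presented alike. A 95% CI may be added if it is labelled descriptive and the text says that significance is judged by p < 0.025.

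The cost is a line of wording in the statistical analysis plan and intervals about 14% wider for the primary outcomes. Sample size, conduct and data collection do not change.

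### The eGFR sensitivity analysis fills deaths with a functioning graft with 49.4, the all-UK mean, although the protocol's own mean for recipients of older-donor kidneys is 41.91

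*Protocol article*

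**What the plan says.** Under Analysis of primary and secondary outcomes, the Protocol article makes the main eGFR comparison complete case: "the primary analysis will be complete case and there will be no imputation for missing values". It then adds a sensitivity analysis with two imputation rules.

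- Graft failure: "if a patient’s graft failed within 12 months, the eGFR at 12 months will be set to the mean value for patients on dialysis", currently 8.5 mL/min/1.73 m².
- Death with function: "If a patient died with a functioning graft within 12 months of transplant", the value is "set to the mean value at 12 months for all UK transplant patients with a functioning transplant at 1 year", currently 49.4 mL/min/1.73 m².

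The justification for the second rule is: "This method assumes that deaths with a functioning graft will occur at random".

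The sample size section for the second primary outcome describes registry data on "all recipients who received a kidney only transplant from deceased donors (DBD and DCD) aged ≥60 years" and reports: "The mean eGFR was 41.91 with an SD of 16.06". The inclusion criteria restrict the analysis to kidneys from deceased donors aged 60 or over, so this is the historical counterpart of the trial population. The article gives no reason for taking the death value from a wider group.

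**The concern.** The imputed value and the assumption behind it refer to different populations. If death with a functioning graft is random among trial recipients, the expected eGFR of those who died is the mean of recipients of older-donor kidneys. Randomness of death does not lead to the mean of all UK transplant patients. The article itself says that graft function worsens as donor age rises, so the wider group can be expected to have the higher mean, and the two reported figures agree with that.

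This is the only eGFR analysis described that brings deaths and graft losses back in. As written, a recipient who dies with a functioning graft is scored as a better-than-average outcome. That is an awkward property in an analysis meant to show whether the complete-case result survives those events.

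**Working it through.** **Inputs.** Death value 49.4 and graft-failure value 8.5 (Analysis of primary and secondary outcomes). Older-donor mean 41.91, SD 16.06, target difference 6, two-sided significance level 2.5%, within-period intracluster correlation 0.06, cluster autocorrelation 0.08, cluster-period size 8 (sample size section). Twenty clusters and five steps (Figure 3 legend). The share of recipients dying with a functioning graft is not given, so the rates below are assumptions.

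**The protocol's own figure.** A generalised least squares variance for six periods, with fixed period effects and random cluster and cluster-by-period effects, gives a standard error (SE) of 1.721. Power is Φ(6/1.721 − 2.241) = 0.89, which reproduces the stated 89%. This SE is used below for scale only.

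**The gap.** 49.4 − 41.91 = 7.49 mL/min, or 7.49/16.06 = 0.47 SD. Under the full target effect the expected intervention mean is 41.91 + 6 = 47.91, and 49.4 − 47.91 = 1.49. The filled value is therefore above the expected mean in both conditions.

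**Effect on the arm difference.** Let Δ be the true difference, and qI and qC the shares dying with a functioning graft under intervention and control. This simplifies the planned mixed model to a comparison of arm means. Filling deaths with 49.4 gives

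D = Δ + qI(7.49 − Δ) − 7.49 qC, which equals Δ(1 − qI) + 7.49(qI − qC).

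Filling with 41.91 gives Δ(1 − qI).

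*No treatment effect.* D = 7.49(qI − qC):
- 1 point: 7.49 × 0.01 = 0.07
- 3 points: 7.49 × 0.03 = 0.22, or 0.2247/1.721 = 0.13 SE
- 5 points: 7.49 × 0.05 = 0.37, or 0.3745/1.721 = 0.22 SE

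*Full target effect.* D = 6 + 1.49 qI − 7.49 qC:

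| qI | qC | Filled with 49.4 | Filled with 41.91 |
|---|---|---|---|
| 5% | 5% | 5.70 | 5.70 |
| 5% | 2% | 5.92 | 5.70 |
| 2% | 5% | 5.66 | 5.88 |

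D exceeds 6 only if qI is more than 7.49/1.49 = 5.03 times qC.

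**Scale against graft failure.** With no treatment effect, a 3-point excess of failures set to 8.5 moves the difference by (41.91 − 8.5) × 0.03 = 1.00. An equal excess of deaths at 49.4 offsets 0.22 of that, about a fifth.

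**The case against.** Most of the opposing case concerns consequence, and much of it stands.

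- The primary test uses no imputation. A reader might infer that the primary eGFR result is biased; the protocol does not support that.
- The gap of 7.49 is larger than the 6 mL/min target, and a reader might conclude that the rule could create or hide the target effect. That compares one patient's filled value with a difference between arm means. The shift in the difference is a few tenths of a mL/min at the assumed rates.
- A reader might infer that the rule always favours the arm with more deaths. Relative to the true difference, that holds only with no treatment effect. At the full effect with 5% and 2% deaths the result is 5.92, below 6, although the intervention arm has more deaths. With equal rates the fall to 5.70 comes from using any single constant; 41.91 gives the same figure.
- The rule does not reward deaths in general. Where the graft failed within 12 months the value is 8.5, which pulls the mean down.
- An excess of deaths would not be hidden. The number surviving to 12 months will be reported, and 12-month patient survival and graft survival are secondary outcomes.
- The two means may not be fully comparable. The 41.91 comes from 2014–2016, uses uncalibrated creatinine, and could not be calculated for 19% of recipients. The formula and period behind 49.4 are not stated, and the article marks it as a current value.

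These points limit the size and direction of the problem. None gives a reason why the mean of all UK transplant patients is the right value for recipients of older-donor kidneys. The mismatch of populations remains even if the exact gap differs from 7.49.

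**Conclusion.** The point holds as a minor one, confined to the sensitivity analysis and to deaths with a functioning graft. The filled value does not follow from the stated at-random assumption and lies about 7.5 mL/min above the value that does, assuming comparable formulas and periods. Each such death raises its arm's mean as long as that mean is below 49.4, which covers both conditions even at the full target effect.

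With no treatment effect, the arm difference shifts by about 0.07 mL/min per percentage point of difference in these deaths. Under a true effect the net movement depends on the rates in both conditions, so no general direction of bias can be claimed. All sizes rest on assumed death rates and on the simple arm-mean calculation.

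**What to change.** Replace 49.4 with the 12-month mean eGFR of recipients of kidneys from donors aged 60 or over who have a functioning graft, calculated with the same formula as the trial outcome. Use one value pooled over conditions. Filling by condition would build the observed difference into the imputed records and largely reproduce the complete-case estimate with too small a standard error.

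Alternatively, impute only graft failures at 8.5 and leave deaths with a functioning graft out, which is consistent with the at-random assumption.

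Either option changes one constant or one line. The registry extract behind 41.91 shows that the data are available. The costs are small: a single filled value slightly understates the variance, as the present rule already does, and leaving deaths out means that the analysis tests graft failures only.

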#### Other analyses

Sensitivity analyses: although access to the urgent pathology service is immediate and preceded by formal education, it is still possible that the response (change in behaviour towards older donors) may be more gradual. To monitor this, a sensitivity analysis which excludes the first 2 weeks following crossover to the intervention arm will be conducted, to observe whether this significantly alters our conclusions.Variation of effect over time: an assessment of how all centres change their behaviour from the time they are introduced to the urgent biopsy service will be performed. This will be evaluated by estimating treatment effects by time since introduction of the intervention.Subgroups: the primary outcome will be replicated for each subgroup separately:DBD donors only;DCD donors only;Donors who are aged >70 years;Centres with a historic low median UK Kidney Donor Risk Index of transplanted DCD kidneys (low risk transplant activity).

Full details of the statistical analyses will be specified in the Statistical Analysis Plan.

#### Health economic analysis

A within-trial and decision model-based economic evaluation will be conducted from the perspective of the National Health Service (NHS), comparing the national histopathology service versus treatment as usual (no biopsy service). The within trial analysis will estimate the cost of the histopathology service including capital investment (eg, scanners), training for centres, staffing and transportation costs, and cost of patient NHS contacts (eg, dialysis, transplant surgery or secondary care contact). Cost data will be extracted from trial records and the UKTR, held by NHSBT. The outcome in the analysis will be the number of patients with a functioning transplant per centre standardised to a 12-month time horizon. The analysis will therefore report the incremental cost per incremental functioning kidney over 12 months.

The within-trial timeframe of 12 months is insufficient to fully capture the differences in costs and outcomes between the study arms. Therefore, a decision model-based economic evaluation will predict demand and supply of kidneys for transplant in the UK, combining cost and outcomes evidence from the trial with other relevant evidence from the literature to determine the incremental cost per quality-adjusted life-year gained from the service. Full details of the economic analyses will be specified in the Health Economics Analysis Plan.

